### Data collection

Data collection in project parts 1 and 2 will be based on clinical assessments and self-reported measures, conducted by formally trained professionals (seven RDHs, and two doctoral students; with the professions RDH and SLP). These professionals have received specific training on data collection and on instructing participants and staff about the intervention; i.e., the swallowing training. The data collection period is 2013–2017.

In project part 1, clinical assessments will record: (a) eating ability and nutritional risk, (b) oral health status, (c) swallowing ability, (d) functional status (i.e., activities of daily living), (e) biometric measures (e.g., body weight and height), medical diagnoses, and planned discharge destinations, based on social service and nursing documentation. Self-reported measures will include: (f) care quality related to oral health and eating, (g) oral HRQoL, and (h) swallowing-related QoL. In project part 2, clinical assessments will record: (a) eating ability and nutritional risk, (b) oral health status, (c) swallowing ability, (d) functional status, and (e) biometrics and where the participant is located at the time. The self-reported measures will include: (g) oral HRQoL and (h) swallowing-related QoL. Table 1 provides an overview of the validated instruments used for the data collection in project parts 1 and 2, and the time points when the assessments will be performed. For detailed information about the instruments, see the primary references shown in Table 1.

**Table 1 Tab1:** Instruments and measures to be implemented for data collection

Instrument	Reference	Outcome	Description	Time point
Katz Index of Activities of Daily Living (Katz-ADL)	[32, 33]	Functionality. Secondary outcome	Clinical assessment tool. Total score range: 1–7 (i.e., A-G), where 1 is “independent” and 7 is “very dependent”.	t1, t2, t3
Minimal Eating Observation and Nutrition Form –version II (MEONF-II)	[23, 24]	Risk of under-nutrition (UN), based on eating ability. Primary outcome	Clinical assessment tool. Total score range: 0 to 8, where 0–2 is no or low UN-risk; 3–4 is moderate UN-risk; ≥5 is high UN- risk.	t1, t2, t3

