Quality of care from a patient’s perspective- modified version (QQP-modified version)	[19, 20]	Quality of care. Primary outcome	Self-reporting tool; 24 items. Each item is rated for both perceived reality (PR) and subjective importance (SI) with a 4-point Likert type scale. The PR range is: 1 (do not agree at all) to 4 (completely agree); the SI range is: 1 (little or no importance) to 4 (very highest importance). For each item, the PR and SI can also be rated ‘not applicable’ (58).	t1
Oral health status	Descriptive	Oral health.Primary outcome	Clinical assessment, which includes: an estimation of oral hygiene; a numeric registration of teeth; the presence of bridges, partial denture, full denture, implants; the number of occluding surfaces; and a record of the need for dental care. Also questions were asked about self-perceived oral health, whether there was an established dental contact, and the time since the most recent dental visit.	t1, t3
Revised Oral Assessment Guide (ROAG)	[25, 26]	Oral health status. Primary outcome	Clinical assessment tool, which includes 9 categories: voice, lips, mucous membranes, tongue, gums, teeth, dentures, saliva, and swallowing. Each category is described and graded on 3-point Likert scale: 1 indicates “healthy or normal condition”, 2 indicates “moderate alterations”, and 3 indicates “severe alterations”.	t1, t3
Oral Health Impact Profile (OHIP-14)	[28, 29]	Quality of life related to oral health. Secondary outcome	Self-reporting tool with 14 items in 7 categories. Each item is estimated on a 5-point Likert scale: 0 indicates “never” and 4 indicates “very often”.	t1, t3
The Swallowing Capacity Test (SCT)	[18]	Swallowing capacity. Primary outcome	A teaspoon test is carried out before the SCT. When signs of aspiration are observed, the SCT is not performed. Clinical assessment: the participant is instructed to drink 150 ml water from a glass as rapidly as possible, but safely, and to stop if any difficulty arises. Swallowing capacity is measured as the amount of water swallowed divided by the time it takes (ml/s). A capacity of ≥10 ml/s is considered normal. Signs of dysphagia will be recorded (e.g., coughing or wet/gurgling voice). When the subject fails the teaspoon test, a SCT score of 0 ml/s will be recorded.	t1, t2, t3

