### Statistical methods

The statistical package, IBM/SPSS®, will be used to perform all data analyses. *P*-values less than 0.05 will be considered statistically significant. Descriptive statistics will be used to describe eating ability, oral health status, swallowing ability, quality of oral care, and swallowing-related QoL, among older individuals admitted to short-term care units. Descriptive statistics will also be used to describe the staffs’ perceptions of care quality. Univariate, bivariate, and multivariable regression (linear and logistic) analyses will be used to evaluate the associations between various dependent and independent variables. The Bonferroni correction will be used when multiple, pair-wise tests are performed on a single set of data, to reduce the chances of obtaining type I errors. Continuous variables will be presented as the mean value and standard deviation; categorical variables will be reported as the median and interquartile range. Differences between groups (e.g., intervention vs. control, older individuals vs. staff) will be assessed with independent sample t-tests (for continuous variables), chi-square tests (for categorical variables), and ANOVA or Kruskal-Wallis (for more than 2 groups).

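### The rule for categorical variables (median and IQR, then chi-square) does not suit nominal data, and it leaves ordinal scores without a rank test when two groups are compared

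*Protocol article*

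**What the plan says.** The Statistical methods section of the protocol article gives one descriptive rule per class of variable: mean and SD for continuous variables, while "categorical variables will be reported as the median and interquartile range". Counts and percentages are not mentioned.

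For comparisons it names "independent sample t-tests (for continuous variables), chi-square tests (for categorical variables"), followed by "ANOVA or Kruskal-Wallis (for more than 2 groups"). The scope is "Differences between groups (e.g., intervention vs. control, older individuals vs. staff"), and both of these examples have two groups. The general significance rule is that "values less than 0.05 will be considered statistically significant".

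The Data collection section lists nominal variables, among them diagnoses and planned discharge destination. Table 1 adds the presence of bridges, dentures and implants. Table 1 also lists ordered scales:

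- Katz-ADL, 1 to 7, labelled secondary.
- MEONF-II, "Total score range: 0 to 8", with three risk bands, labelled primary.
- ROAG, labelled primary: "Each category is described and graded on 3-point Likert scale".
- OHIP-14 (14 items) and SWAL-QOL (44 items), rated on five points, labelled secondary.
- The quality-of-care items, rated on four points, labelled primary and measured at t1 only.

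Nowhere does the article say which of these scales count as continuous and which as categorical.

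**The concern.** One word, categorical, carries a summary that suits only ordered data and a test that suits unordered data. Neither reading makes both rules right.

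- **Nominal reading.** A median and IQR of diagnoses or discharge destinations cannot be formed.
- **Ordinal reading.** The summary is sensible, and this is what the median rule suggests was meant. But chi-square gives the same result however the levels are ordered, so it discards the information that makes the score useful.

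The authors did provide a rank method, but restricted it to more than two groups. The randomised comparison has two. At stake is power for any ordinal outcome of part 2 that is put through chi-square. There is also an open choice between t-test and chi-square that could be made after the data are seen.

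**Working it through.** **Inputs from the protocol article.** Part 2 needs at least 22 per group, with SD of the SCT change 3 ml/s, difference 2.8 ml/s, power 80% and type I error 2.5% (Sample size calculation). The general level is 0.05 (Statistical methods). The number of levels per scale comes from Table 1.

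**Step 1: the plan's own figure.** With a two-sided 2.5% level and the normal approximation:

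n = 2 (z₀.₉₈₇₅ + z₀.₈₀)² SD² / difference² = 2 × (2.241 + 0.842)² × 9 / 7.84 = 2 × 9.505 × 1.148 = 21.8, so 22 per group.

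The stated 22 is reproduced. The standardised effect is 2.8 / 3 = 0.93 SD. The article gives no power for any ordinal outcome, so the rest rests on assumptions.

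**Step 2: why order matters.** A 2 × k table spends k − 1 degrees of freedom where a rank test spends one. Take a noncentrality that gives 80% power on 1 df at 5%: (1.960 + 0.842)² = 7.85. The same noncentrality gives 71% power on 2 df, 60% on 4, 52% on 6 and 47% on 8.

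**Step 3: simulation at 22 per arm.** A normal latent variable is shifted between arms and cut into k ordered levels, with 3,000 runs per setting and a two-sided 5% level. The shifts of 0.5 and 0.8 SD are assumed. The shift of 0.93 SD is borrowed from the SCT calculation. Levels are equally likely in controls, or unevenly distributed as a sensitivity check. Participants are treated as independent. Entries are power of Pearson chi-square → Mann-Whitney with equally likely levels.

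| Levels | 0.5 SD | 0.8 SD | 0.93 SD | Relative loss, even | Relative loss, uneven |
|---|---|---|---|---|---|
| 2 | 24→24% | 51→51% | 64→64% | 0 | not run |
| 3 (ROAG grade, MEONF-II band) | 23→29% | 53→63% | 66→75% | 12–21% | 12–24% |
| 5 (single five-point item) | 18→34% | 45→68% | 58→81% | 29–48% | not run |
| 7 (Katz-ADL) | 14→34% | 35→70% | 48→81% | 41–58% | 42–62% |
| 9 (MEONF-II 0–8) | 11→33% | 29→69% | 40→83% | 52–67% | 52–69% |

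Relative loss is 1 − chi-square power / Mann-Whitney power. For seven levels it is 1 − 0.144 / 0.340 = 58% at 0.5 SD and 1 − 0.480 / 0.814 = 41% at 0.93 SD. At a 2.5% level the losses with equally likely levels are larger: 17–28%, 40–60%, 53–66% and 64–75% for 3, 5, 7 and 9 levels.

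**Step 4: a second model.** A proportional-odds shift on seven levels (4,000 runs, control probabilities 0.10 and six of 0.15) gives 10 against 25% at odds ratio 2, 23 against 51% at 3, and 39 against 71% at 4. The relative losses are 1 − 10/25 = 60%, 1 − 23/51 = 55% and 1 − 39/71 = 45%, in line with step 3. Type I error was 4.3% for chi-square and 4.6% for Mann-Whitney.

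**Step 5: the t-test route.** In the step 3 simulations the t-test on the same scores had power within about 2 points of Mann-Whitney.

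**The case against.** The strongest defence is that no scale is classed as categorical. An analyst may treat the scores as continuous, use the t-test, and lose almost nothing. A median of diagnoses cannot be computed, so counts would be reported in practice. The first part stands: the power loss is conditional. It does not rescue the text, because the article fixes a rule and does not merely omit detail, and that rule cannot be followed for nominal data. The unstated class of each scale is itself part of the problem.

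Several stronger readings are tempting, and the documents do not support them.

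- *A reader might infer that the ordinal secondary outcomes in general lose about half their power.* Table 1 labels three outcomes secondary. Of these, only Katz-ADL is plainly one seven-level score. OHIP-14 and SWAL-QOL are multi-item scales whose totals may go to the t-test. Three-level items lose far less. The heaviest loss would fall on MEONF-II 0–8, which Table 1 labels primary.
- *A reader might carry the 22-per-arm figures over to the quality-of-care items.* These are measured at t1 only, and the project plans about 400 older people and 200 staff. With four levels (assumed probabilities 0.1, 0.2, 0.3, 0.4), chi-square against Mann-Whitney gives 55 against 72% at odds ratio 1.5, 83 against 94% at 1.75, and 96 against 99% at 2. That is a loss, but at most 1 − 55/72 = 24%.
- *A reader might expect sparse cells to produce false positives.* With seven levels evenly used, the expected count is 22/7 = 3.1, below the usual 5, yet type I error was 4.3%.
- *A reader might say the analysis could not show which arm did better.* Chi-square has no direction, but the required median and IQR would show it for an ordinal score.
- *A reader might think the main result of part 2 is at risk.* The Sample size calculation section bases it on the change in SCT in ml/s, which is continuous.

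**Conclusion.** The point holds in a limited form. The descriptive rule is wrong for nominal variables under any reading. For two-group comparisons the plan offers ordinal scores only chi-square if they count as categorical, and it reserves its rank test for more than two groups.

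If ordinal scores are handled as categorical, the relative loss of power at 22 per arm and the 5% level is about 12–24% for 3 levels, 29–48% for 5 and 41–69% for 7 to 9. These sizes rest on the assumed shifts and level distributions, and on comparing the score itself between arms. They ignore clustering by care unit, so they show relative loss and not the power the trial will have. Nothing is lost for two-level variables, almost nothing for scores analysed by t-test, and the SCT change is untouched. The validity of the test is not in question; the cost is power and clarity. The text should be corrected, but the design does not depend on it.

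**What to change.** Replace the rule for categorical variables with three statements:

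1. Nominal variables are reported as n (%) and compared with chi-square, or Fisher's exact test where cells are sparse.
2. Ordinal scores are reported as median (IQR). Two groups are compared with Mann-Whitney or a proportional-odds model, and more than two with Kruskal-Wallis.
3. Each Table 1 scale is assigned to a class (nominal, ordinal or continuous), including whether MEONF-II is analysed as the 0–8 score or as risk bands, and whether OHIP-14 and SWAL-QOL are analysed as totals or by item.

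The cost is a few sentences, fixed before the comparative analysis. No new data and no change of design are needed, and the software already named can run these methods. Whether to model the care unit or adjust for the baseline score is a separate matter that this correction does not settle.

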**Methods/Design:**

This project consists of two parts, which will be performed in five Swedish counties. It will include approximately 400 older individuals and 200 healthcare professionals. Part 1 is a cross-sectional, descriptive study of older people admitted to short-term care. Subjects will be assessed by trained professionals regarding oral health status, oral HRQoL, eating and nutritional risk, and swallowing ability. Swallowing ability will be measured with a teaspoon test and a swallowing capacity test (SCT). Furthermore, subjects and staff will complete a questionnaire regarding their perceptions of care quality.

Part 2 is a cluster randomized intervention trial with controls. Older participants with dysphagia (i.e., SCT <10 ml/s, measured in part 1) will be recruited consecutively to either the intervention or control group, depending on where they were admitted for short-term care. At baseline, all subjects will be assessed for oral health status, oral HRQoL, eating and nutritional risk, swallowing ability, and swallowing-related QoL. Then, the intervention group will receive 5 weeks of training with an oral screen for neuromuscular training focused on orofacial and pharyngeal muscles. After completing the intervention, and at six months post-intervention, all assessments will be repeated in both study groups.

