### Design and setting

The SOFIA project consists of two main parts; part 1 is a descriptive, cross-sectional study (aims *i* and *ii*), and part 2 is a cluster randomized, controlled trial (aim *iii*).

Data collection will take place in 32 short-term care units, located in five Swedish counties, in both rural and urban areas. The short-term care units are diverse in organization and staffing; they may be one section of a care home or an independent short-term care unit.

Participating short-term care units will be selected, based on informed consent from the heads of social welfare services and unit managers; the number of beds; the estimated number of discharges per month; and the geographic location. The sample in part 1 will comprise approximately 400 older participants. All participants will be assessed at baseline, and participants that exhibit low swallowing capacity (i.e., <10 ml/s) will be asked to participate in the interventional part of the study (part 2). In part 2, participating older persons will, after informed consent, be randomized into either the intervention or the control group, based on where they were admitted for short-term care. In addition to the baseline assessments, all participants in part 2 will be assessed after the intervention is completed (5 weeks) and 6-months post-intervention. The follow-up assessments will be conducted at the study participant’s location (e.g., in the short-term care unit, in the individual’s own home, or in a care home, where the older person resides at that time).

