The Swallowing Quality of life Questionnaire (SWAL-QOL)	[30, 31]	Quality of life related to swallowing. Secondary outcome	Self-reporting tool with 44 items. Each item is rated on a 5-point Likert scale. Range: 1 “least favorable state” to 5 “most favorable state”. An additional 3 items are included for rating different types of food and drink consistencies and health status. These are rated on a 5-point Likert scale.	t1*, t2, t3

t1 = baseline; t1* = only older individuals with swallowing capacity <10 ml/s at baseline; t2 = immediately after the 5 week intervention; t3 = 6 months post-intervention

Data on external, objective care conditions, such as staffing, number of beds, length of stay, and prevalence of overcrowding, will be collected from the unit manager at each short-term care unit.

The nursing staff members’ perceptions of the quality of oral care and eating-related issues will be measured with a modified version of the Quality of care from a patient’s perspective questionnaire (QPP-Staff) [19, 20]. These data will be collected during a workplace meeting.

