### Methodological considerations

Methodological and ethical problems were previously reported as challenges that explained the lack of empirical studies conducted in the short-term care context [16]. Therefore, the present project includes several strategies to increase the probability of succeeding and to strengthen the results, as follows: (1) only participants with sufficient cognitive capacity are included; (2) older individuals in end-of-life care are excluded; (3) multiple short-term care units are included, housed in various settings and located in different parts of Sweden; (4) a cluster randomization trail design is implemented; (5) both clinical and self-reported assessments are considered; (6) the data collectors are professionals that hold relevant clinical experience in communicating with older individuals and assessing their oral health and swallowing ability; in addition the research team has experience in the care context, where the data will be collected.

By minimizing methodological and ethical challenges, our results, regarding oral health status, swallowing, eating ability, and nutritional risk, might not be representative of all older people in short-term care, e.g., individuals in the highest risk categories will not be included. Other methodological challenges might arise when performing the intervention study with late follow-up assessments (six months). These challenges include accessing information on where the participant is located at the time of the follow-up; managing the high risk of drop-out, due to mortality, in the study population; and recruiting for part 2 of the study. The latter problem is expected, because older people might have low motivation to participate in swallowing rehabilitation, due to fatigue, or because they have adapted to their situation and find no use in training [6].

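### Part 2 assigns arms by care unit, but the stated intervention-versus-control test treats participants as independent, so the 2.5% type I error is not held

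*Protocol article*

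**What the plan says.** The design is stated consistently. The abstract says: "Part 2 is a cluster randomized intervention trial with controls". Design and setting says that participants will "be randomized into either the intervention or the control group, based on where they were admitted for short-term care". Methodological considerations lists it among the strengths: "a cluster randomization trail design is implemented". The setting is also given: "Data collection will take place in 32 short-term care units, located in five Swedish counties". The same section describes the units as differing in organisation and staffing.

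The analysis is in Statistical methods: "Differences between groups (e.g., intervention vs. control, older individuals vs. staff) will be assessed with independent sample t-tests (for continuous variables"). Categorical variables get chi-square tests, and comparisons of more than two groups get ANOVA or Kruskal-Wallis. Linear and logistic regression are named for associations, without further detail.

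Sample size calculation sets the type I error at 2.5% for the primary endpoint, so as to keep 5% overall. It assumes a standard deviation of 3 ml/s for the change in swallowing capacity (SCT) and a difference of 2.8 ml/s, and arrives at 22 completers per group for 80% power. The article mentions no ICC, design effect, random unit effect, robust standard error or cluster-level summary.

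**The concern.** When a whole unit is allocated to one arm, part of the difference between arms is difference between units. A two-sample t-test on individuals estimates its error from the spread between people and does not count the shared unit component in full.

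A shared component is plausible here. Control care follows each unit's own routines, unit staff help participants who cannot train alone, and the Background itself names differing skill mix and staffing as a source of confounding.

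At stake is the primary SCT comparison. Its p-value would be too small and its confidence interval too narrow, by an amount the plan gives no means of judging.

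**Working it through.** **1. The plan's own figure.** Two independent means, two-sided alpha 0.025, power 80%:

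n per group = 2 × (2.2414 + 0.8416)² × (3 / 2.8)² = 21.8, rounded up to 22.

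The stated 22 is reproduced by the formula for individually randomised participants, that is, with a design effect of 1. Planning and analysis therefore make the same assumption.

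**2. Inputs for the check.** From the article: 32 units, 22 completers per arm, nominal 2.5%. Assumed, because the article gives no value: ICC 0.05, 0.10 or 0.20; 32 or 16 units contributing to part 2, half per arm; and even or uneven spread of participants over units. Uneven spread is represented by exponentially distributed unit weights.

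**3. Formulas.** Design effect DE = 1 + (m − 1) × ICC, where m is the size-weighted mean number of participants per unit. The true standard error is √DE times the one the t-test uses. With 42 degrees of freedom the two-sided 2.5% critical value is 2.325, so the true error is approximately 2 × P(T₄₂ > 2.325 / √DE).

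Values of m:
- Even over 32 units: 44 / 32 = 1.375.
- Uneven over 32 (16 per arm): 1 + 21 × 2/17 = 3.47, where 2/17 is the expected sum of squared weights.
- Uneven over 16 (8 per arm): 1 + 21 × 2/9 = 5.67.

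**4. Results for ICC 0.05 / 0.10 / 0.20.**

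| Spread | DE | True error at nominal 2.5% |
|---|---|---|
| Even, 32 units | 1.02 / 1.04 / 1.08 | 2.6% / 2.8% / 3.0% |
| Uneven, 32 units | 1.12 / 1.25 / 1.49 | 3.4% / 4.4% / 6.4% |
| Uneven, 16 units | 1.23 / 1.47 / 1.93 | 4.2% / 6.2% / 10.2% |

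Simulating the t-test on 22 + 22 participants agrees: 2.7% to just over 3% for even spread (3.5% in one run at ICC 0.20, because 22 people cannot be divided equally over 16 units), 3.3–7.0% for uneven spread over 32 units, and 4.1–11.0% for uneven spread over 16.

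**5. Interval width and power.** A correct interval is wider by √DE: 1% to 4% for even spread over 32 units, and √1.93 = 1.39, nearly 40%, in the worst case shown. Power with 22 per group is Φ(2.8 / (3 × √(2 × DE / 22)) − 2.2414). This gives 80% at DE = 1, 77–80% for even spread, 61–75% for uneven spread over 32 units, and 49–71% for uneven spread over 16. Degrees-of-freedom corrections for few units would lower these further.

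**6. Part 1, for comparison.** 400 / 32 = 12.5 per unit, so DE = 1 + 11.5 × ICC = 1.58 at ICC 0.05 and 2.15 at ICC 0.10. For a predictor that varies only between units and is tested at 5%, the true error is 2 × P(Z > 1.96 / √DE) = 12% and 18%.

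**The case against.** **Size in part 2.** The ICC, the number of contributing units and their sizes are all assumptions. With 44 completers spread evenly over the 32 stated units there would be little more than one person per unit, and the t-test would be nearly correct. This stands: the direction of the error is certain for a positive ICC with more than one participant per unit, but its size is not. A reader might infer that the error rate is grossly inflated. The documents do not show that; the high figures need few contributing units and a high ICC.

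**Condensed article.** An article may leave model detail to a fuller plan. That would excuse silence, but the article is not silent: it names this comparison and assigns it a test that does not fit the randomisation.

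**Part 1 regressions.** A reader might infer that these share the fault. The article says only that they are linear and logistic, and it does not exclude a unit effect. Unit characteristics ("such as staffing, number of beds, length of stay, and prevalence of overcrowding") will be collected, but nothing commits them to a regression as predictors, and the 12–18% does not apply to person-level associations.

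**Older people versus staff.** This comparison also gets an independent t-test, and a reader might infer the same inflation. The two groups come from the same units, so the shared unit effect largely cancels in the difference. Simulated error was 4.1–5.1% at nominal 5% with ICC 0.10, which is about nominal or slightly conservative.

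**Conclusion.** The point holds for part 2. The stated test of intervention against control contradicts the stated cluster randomisation, and nothing else in the article corrects for it. Under the assumptions above, the true error at nominal 2.5% runs from just above nominal (thin, even spread over 32 units) to about 11% (uneven spread over 16 units, ICC 0.20). The 22 per group rests on the same assumption of no clustering.

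Because this is the primary comparison and the correction is cheap, it should be made before analysis. For part 1 the point is a minor note, confined to any analysis that uses unit-level factors as predictors. It does not extend to the comparison of older people with staff.

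**What to change.** In Statistical methods, replace the independent-sample t-test for intervention versus control by a linear mixed model (SPSS MIXED, within the software already named). Specify arm as a fixed effect, a random intercept for care unit, and small-sample degrees of freedom (Satterthwaite or Kenward-Roger). The model can also carry age, which Measurement tools says must be considered as a covariate for the SCT.

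For categorical outcomes, or where units hold too few participants to fit a random intercept, specify a cluster-level or cluster-robust analysis with a small-sample correction.

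In Sample size calculation, state that 22 per group and 80% power assume no clustering, and give power over a stated range of ICC and unit size.

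For part 1, add one sentence: where unit-level factors serve as predictors, the model accounts for the 32 units.

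The cost is rewording and some extra analysis work. Intervals will widen, slightly if participants spread thinly over many units and by up to about 40% if few units contribute and the ICC is 0.20. The change of analysis itself needs no extra participants, but restoring 80% power under clustering might.
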